### Pharmacokinetics analysis

Plasma concentrations will be used to build a population PK models to evaluate the effects of NAC on the distribution, metabolism, and excretion of MDR-TB drugs.

### Mycobacterial characterization

Descriptive summary statistics of *M. tuberculosis* isolate susceptibility will be presented.

### Interim analyses

There will be no interim analysis, apart from approximately 6-monthly safety review by the DSMB (see below). The final analysis will be performed when the last participant has completed the last trial procedure. There will be database lock, data analysis, and trial reports generated from this trial.

### Methods in analysis to handle protocol non-adherence and any statistical methods to handle missing data

We will report clearly any missing data and deploy multiple imputations under the missing at random assumptions for the missing outcomes or covariates, which we anticipate to minimal and not systematic.

### Plans to give access to the full protocol, participant level-data and statistical code

Data will be available and will be accessed in appropriate data management portals, yet personal information that will identify the participants will not be shared.

## Oversight and monitoring

### Composition of the coordinating center and trial steering committee

There will be a Clinical Trial Management Group (CTMG) which will undertake all sponsorship responsibilities to ensure that the conduct of the clinical trial comply with Medicines for Human use Regulations of 2004 and subsequent amendments for regulated trials. Five members of the CTMG are composed with the sponsor-investigator, the co-investigator also serves as pharmacotherapy expert, the clinical microbiologist, study doctor also a PhD trainee on clinical trials, and quality assurance largely focusing on safety who has a decade experience of working in clinical trials but also attached for one year at Novartis Pharma under the EDCTP Clinical Research and Development Fellowship. The CTMG will ensure the right, safety, dignity, and well-being of the participants are protected and take priority over other interests while the data generated are reliable and robust.

### Composition of data safety monitoring board (DSMB), its role and reporting structure

A DSMB with three members will be appointed with a primary responsibility of an act in an advisory capacity to the sponsor to safeguard the interests of trial subjects by monitoring subject safety, assess subject risk versus benefit, assess data quality and general evaluation of the trial progress. DSMB activities will be delineated in a term of agreement that will define the membership, responsibilities and the scope and frequency of data reviews. The DSMB will operate on a conflict-free basis independently of the sponsor and the trial team. It will comprise 3 voting members. The DSMB will have an organisational meeting prior to commencement of the trial. The DSMB will meet approximately every six months and at least annually when it will review unblinded data during a closed session. The sponsor or the DSMB may convene ad hoc meetings if safety concerns arise during the trial. After its assessment, the DSMB will recommend to the sponsor continuation, modification or termination of the clinical trial.

### Adverse event reporting and harms

Adverse events will be collected by the investigator from the time a subject sign the Informed Consent Form through to their end of follow-up visit. Participants that will be early withdrawn, will only have SAEs collected at the time of withdrawal. Any AE (serious or non-serious) observed by the investigator or reported by the subject will be recorded on the Adverse Event Case Report Form. The investigator will review each AE and assess its severity and relationship to drug treatment based on all available information at the time of the completion of the case report form. AE with relationship with drug treatment will be termed as ADRs and severity grading will be according to the CTCAE.

In the case where an overall diagnosis cannot be made, each specific sign and/or symptom will be recorded as individual AEs. Documentation of the date of onset, and stop date (duration) if applicable will be done. The AEs will also be described in severity, and action taken with IMP while concurrently describing the action taken to the participant. The outcome and relationship to IMP will be recited. Also, the occurrence and seriousness of the AEs will be documented.

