### Data collection and management

All case record forms (CRF) both electronic and hard copy pages will be completed for every participant receiving any amount of IMP. Clinical information will be captured in eCRF while laboratory information will be captured in hard copy CRF. For screening failure participants, a screening failure eCRF will be completed. For subjects who are prematurely withdrawn, the visits up to withdrawal plus the withdrawal and follow-up visits need to be completed.

Source documents are defined as all information in original records and certified copies of original records of clinical findings, observations, or other activities in a clinical trial necessary for the reconstruction and evaluation of the trial. Source documents will include, but are not limited to, progress notes, electronic data, screening logs, and recorded data from automated instruments.

All source documents pertaining to this trial will be maintained by the investigators. Source documents will be available for trial-related monitoring, audits, Institutional Review Board (IRB) review and regulatory inspections providing authorized persons direct access to source documents.

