## Statistical methods

### Statistical methods for primary and secondary outcomes

The primary efficacy analysis will be conducted using laboratory measurement. Analysis that will be performed includes both Modified Intent to Treat (MITT) defined as analysis of all randomised participants and a Per Protocol (PP) defined as comparison of three arms; control with either 900 mg OD or 900BD or both intervention arms in participants who completed the treatment originally allocated.

The difference in the proportion of patients with ADRs (as defined by the primary efficacy endpoint) between each treatment arm and control arm will be calculated with 95% confidence interval using standard methods**.** In addition, hearing threshold level will be analysed over time using mixed effect models to account for the longitudinal nature of the data. Mean differences between arms in change from baseline (with 95% confidence intervals) will be derived from the fitted model.

The incidence of severe adverse drug reactions as defined by Common Terminology Criteria for Adverse Event (CTCAE) will be calculated in percentage of affected individuals in each arm during the exposure time period of 6 months and the relative risks will be estimated. Time to stable conversion in both phenotypic and molecular (TB molecular bacterial load assay) MTB monitoring methods will be calculated and compared in each arm using adjusted and unadjusted hazard ratio with log-rank test. Furthermore, the rate of patients in each arm converting to negative sputum culture at 4 or 6 or 8 months after treatment initiation will be estimated. Kaplan-Meir estimator will be used to estimate the proportion of patients converting to negative culture and MBLA by specific time.

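### Adverse event reporting rules conflict for early-withdrawn participants: an SAE-only rule can leave their ADR status unknown, although the protocol already requires their withdrawal and follow-up visits

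*Protocol article*

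**What the plan says.** Three statements in Adverse event reporting and harms bear on the point.

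- The collection window: "Adverse events will be collected by the investigator from the time a subject sign the Informed Consent Form through to their end of follow-up visit".
- The rule for early withdrawals, which follows directly: "Participants that will be early withdrawn, will only have SAEs collected at the time of withdrawal".
- The general recording rule, which comes next: "Any AE (serious or non-serious) observed by the investigator or reported by the subject will be recorded on the Adverse Event Case Report Form".

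The same section defines the endpoint event: "AE with relationship with drug treatment will be termed as ADRs and severity grading will be according to the CTCAE". Seriousness is not part of that definition.

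Data collection and management adds, for the same participants: "For subjects who are prematurely withdrawn, the visits up to withdrawal plus the withdrawal and follow-up visits need to be completed".

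On the analysis side, Trial design names the occurrence of ADRs at any time during MDR-TB treatment as the primary endpoint. Statistical methods for primary and secondary outcomes reports severe ADRs, graded by CTCAE, as the "percentage of affected individuals in each arm during the exposure time period of 6 months and the relative risks will be estimated". It takes as one analysis set "Modified Intent to Treat (MITT) defined as analysis of all randomised participants". For missing data, the plan is to "deploy multiple imputations under the missing at random assumptions for the missing outcomes or covariates".

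**The concern.** The adverse event section gives site staff two instructions for one participant: record every event, and record only serious ones. Nothing says which prevails. If staff follow the narrower one, the visits take place but part of the endpoint information from them is not captured.

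The restriction is by seriousness, whereas the endpoint is by relatedness and, for the severe ADR analysis, by CTCAE grade. These are different scales. A laboratory abnormality can be of severe grade and drug-related without being serious. Such an event, first found at a withdrawal visit, falls outside an SAE-only rule yet belongs in the severe ADR percentage.

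At stake is the ADR status of withdrawn participants, who stay in the denominator because the modified intent-to-treat set holds everyone randomised. An analysis plan can choose how to treat an unknown status, but it cannot restore an event or a relatedness judgement that nobody recorded. The Outcomes section calls feasibility metrics primary and lists adverse event proportions as secondary endpoints, so the rank of the ADR endpoint is itself unclear. The point does not depend on that rank, since the proportions are estimated either way and are meant to inform a larger trial.

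**Working it through.** **Step 1: compare the rules for one case.** Take a participant who withdraws early, still attends the withdrawal visit, has no ADR recorded so far, and is found there to have a non-serious, drug-related event.

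| Rule (Protocol article) | Is the event recorded? |
|---|---|
| Collection window to end of follow-up | Yes |
| SAE-only sentence for early withdrawals | No |
| General rule, any seriousness | Yes |
| Visits required after withdrawal (Data collection and management) | The visit takes place; event scope is not addressed |

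The first three rows are from one section and do not agree. The SAE-only sentence is specific and contains the word *only*, and the general rule after it does not say that it overrides the exception. Under the literal exception the event does not reach the adverse event form. It is then not assessed for relatedness and cannot be classed as an ADR.

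**Step 2: who could be affected.** Sample size gives 20 per arm, 60 in total, with a 10% withdrawal or non-evaluable rate and 66 recruited.

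- The plan's figure reproduces as 60 × 1.10 = 66. Dividing instead, 60 / 0.90 = 66.7, gives 67. The figure is not in dispute here.
- Allowance: 66 − 60 = 6 participants, or 6 / 66 = 9.1%.
- With 1:1:1 allocation and an even spread: 2 of 22 per arm (2 / 22 = 9.1%).

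The 10% combines withdrawal with non-evaluability, and the retention section reports up to 100% retention at the site. A working range is therefore 0 to 2 per arm.

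**Step 3: the largest shift in an arm's percentage.** Assume the participant is counted as unaffected, a rule the protocol does not state.

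- One missed first ADR: 1 / 22 = 4.5 points.
- Two: 2 / 22 = 9.1 points.

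The shift is zero for a participant who already has an ADR recorded, or whose event is an SAE collected at withdrawal. (For the severe ADR percentage, the earlier record must be of a severe ADR.) Imputation would reduce the shift in expectation.

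**Step 4: scale against sampling error.** For a difference between two arms of 22 with equal risk p, the 95% half-width is 1.96 × √(2p(1 − p)/22). The protocol gives no ADR risk for this population and regimen, so p is an assumption.

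| Assumed p | Half-width |
|---|---|
| 0.20 | 23.6 points |
| 0.30 | 27.1 points |
| 0.40 | 29.0 points |

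Even two missed cases in one arm move the estimate by less than half of the smallest half-width (9.1 against 23.6).

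**The case against.** The strongest reply is that the sentence on recording events of any seriousness governs, so nothing is lost. That reading is possible, which is why the point is an inconsistency and not a demonstrated loss. But if it is right, the SAE-only sentence does nothing and should still be removed.

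A reader might infer that Data collection and management flatly contradicts the adverse event section. It does not. One says which visits are completed and the other which events are collected, and a visit can be completed with a narrower scope. The inconsistency lies within the adverse event section; the visit requirement shows only that the missing information could be had without extra contact.

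A reader might also infer that severe laboratory ADRs are lost altogether. The documents do not support that. Laboratory results go on a separate form, and if tests are drawn at those visits the values can be graded later. Whether they are drawn depends on the schedule of events, which is not shown. What would still be missing is the investigator's judgement of relatedness, and any non-laboratory event.

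The restriction might be deliberate, out of respect for someone who has opted out of research. That holds for a participant who refuses contact, and the fix keeps it. It does not explain limiting the record of a participant who attends. An article may leave detailed collection rules to the full protocol, but this rule is stated, so it is not a matter of omitted detail.

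Finally, the affected group is narrow. The participant must withdraw, have no relevant ADR already recorded, and have a first one that is non-serious and found at or after withdrawal, in a trial with daily assessment. This stands, and it sets the priority.

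**Conclusion.** The point holds as an internal inconsistency in Adverse event reporting and harms. Followed literally, the SAE-only sentence leaves some withdrawn participants with unknown ADR status, to be imputed under missing at random or assumed absent.

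The size is small: 0 to 2 participants per arm of 22, at most 4.5 points each, against a half-width of 24 to 29 points. This assumes that the 10% allowance is spread evenly, that these participants would be counted as unaffected, and that ADR risk is 20% to 40%. The 4.5 and 9.1 point figures are upper limits, not expected values.

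A reader might infer bias in favour of NAC, on the idea that intolerance leads to withdrawal and then to unrecorded events. The documents do not support this. The rule applies to all three arms, and Interventions lists stopping trial medication for NAC-related serious events separately from withdrawing from the research. No direction between arms is claimed.

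This is a cheap improvement of minor priority.

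**What to change.** In Adverse event reporting and harms, replace the SAE-only sentence with:

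> Participants withdrawn early who still consent to visits will have all AEs, serious and non-serious, collected at the withdrawal and follow-up visits; those who withdraw consent to all contact will have AEs recorded up to that time.

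This makes the section consistent with itself and uses the visits that Data collection and management already requires.

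The cost is a short protocol amendment, plus completing the adverse event form at those visits. If the change is judged to affect participant safety or welfare, the protocol's amendment rule requires ethics and regulatory submission before implementation. No new visits, tests or participants are needed. Recruitment was in progress at publication, so the change helps only participants who withdraw after it takes effect.

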## Primary objective

To explore the preliminary evidence on the protective effect of NAC through assessing the development of clinical or laboratory-based adverse drug reactions (ADRs) at any frequency during the first six months of local standard of care MDR-TB treatment among patients receiving NAC at a dose of 900 mg daily or 900 mg twice a day compared to those patients treated with the standard of care regimen and placebo.

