### Interventions

We will use n-acetylcysteine (NAC) 900 mg in the effervescent tablet preparation as study drug. NAC is manufactured by BioAdventex Pharma Inc., Canada, based on good manufacturing practice standards. One intervention group will receive NAC at a dose of 1800 mg divided twice daily with second line MDR-TB drugs and another intervention group will receive NAC at a dose of 900 mg second line MDR-TB drugs. The control group will receive only second line MDR-TB drugs.

Participants will stop the use of trial medications if there will be any serious adverse events related to the use of NAC for instance allergic reactions or if a participant opts to withdraw from continuing with research participation.

Study nurses will be responsible for observing the participants taking the investigational medicinal product (IMP) during the treatment phase. Study nurses will provide the participants daily IMP and will document administration in the IMP treatment adherence chart. The site trial pharmacist/delegated dispenser will be responsible for dispensing the IMP. Accurate accountability records will be kept by the site to assure that the IMP will not be dispensed to any person who is not a subject under the terms and conditions set forth in this protocol, i.e., delivery to site, inventory at site, use by subject, destruction etc. The investigator/designee will immediately inform the sponsor of any quality issues arising with respect to the IMP. The sponsor will take whatever action is required should such a situation arise. The investigator undertakes to use the IMP only as indicated in this protocol.

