### Concealment mechanism

This is an open label study. Both the research participants, the investigator team and health care providers will be aware of the assignment. To prevent selection bias by facilitating enrolment of the comparable participants in each arm, allocation concealment will be ensured. Participants will complete all baseline measurements prior to release of the randomization code. A computer-generated randomization numbers will be printed. For every randomization number a code for a treatment will be assigned.

Primary endpoint (ADRs) will be measured by both clinical assessment and laboratory measurements. To avoid ascertainment bias in the measurement of other endpoints such as adverse events, or performance bias in decision to discontinue or modify treatment, or exclusion/attrition bias in the decision to withdraw from the trial or exclude a participant from analysis, blinding will be implemented. Blinding will be at two levels; the trial participants and health care providers. Health care providers include outcomes assessors (physicians and technicians such as aaudiologists), data collectors, laboratory staff, nurses, and pharmacists.

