### Assignment of interventions

This is an open label thus research participants and the investigator team and health care providers will be aware of the assignment. The later includes clinicians, and data collectors.

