## Discussion

This trial is part of the clinical trial capacity development in Tanzania. To our knowledge, this is the first registered trial to examine the protective effect of NAC on occurrence of ADRs in MDR-TB patients treated with current WHO recommended regimens that prioritize bedaquiline, fluoroquinolones, linezolid, and clofazimine. While this new prioritization removes some renal and hearing loss potential if the injectable aminoglycoside is withheld, there remains considerable risk for hepatoxicity from the combination of bedaquiline, clofazimine and a fluoroquinolone, as well as linezolid related cytopenias and neuropathy. Severe ADRs are independently morbid, but resulting treatment interruptions can also amplify *M. tuberculosis* drug-resistance which is particular concern for loss of efficacy of the novel drugs such as bedaquiline [35]. NAC has been recommended as an adjuvant therapy in certain TB and non-TB settings but currently few programmes have adopted this approach in part due to lack of evidence. NAC trials conducted in DS-TB showed not only a protective effect in DILI but also a delayed onset and hastened resolution of DILI if it did occur [36]. Furthermore, a large cohort study revealed that patients that received pulmonary TB treatment and NAC had a substantial reduction in 90-day all-cause mortality compared to those that did not receive NAC [37].

While NAC may provide an opportunity of reducing severe ADRs, it will be important to determine if NAC causes any adverse events independent of the MDR-TB regimen. A pooled analysis of 83 studies (*N* = 9988) that did not include people treated for MDR-TB described the safety of administration of NAC for > 6 weeks. Important adverse events included the gastrointestinal intolerance such as nausea, vomiting, abdominal pain which increased 1.4–2.2 times compared to those that did not get NAC [22]. Given this potential, and the fact that NAC has not been trialed in within a patient population on current WHO recommended medication regimens for MDR-TB, there is clinical equipoise for our proposed trial design.

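### The ADR definition does not say which drug's reactions count, leaves attribution to staff who know the arm, and conflicts with the laboratory-based efficacy analysis, so NAC's own gastrointestinal effects may dilute the comparison

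*Protocol article*

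**What the plan says.** **Definition and assessor.** Under Adverse event reporting and harms, "The investigator will review each AE and assess its severity and relationship to drug treatment", and then "AE with relationship with drug treatment will be termed as ADRs". The drug is not named. The same section records a second relationship for each event: "The outcome and relationship to IMP will be recited". Nothing says how the two judgements combine when the ADR endpoint is formed.

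**Knowledge of the arm.** Assignment of interventions says "This is an open label thus research participants and the investigator team and health care providers will be aware of the assignment". Concealment mechanism opens by calling the study open label, yet later says "Blinding will be at two levels; the trial participants and health care providers", and lists outcome assessors among those providers. Under Interventions, "The control group will receive only second line MDR-TB drugs"; no placebo is described there, although the Primary objective mentions one.

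**What is compared.** The Primary objective concerns "development of clinical or laboratory-based adverse drug reactions (ADRs) at any frequency" in the first six months. Concealment mechanism says ADRs are measured both clinically and by laboratory. Statistical methods for primary and secondary outcomes compares the proportion of patients with ADRs in each NAC arm with control, but the same section says the main efficacy analysis uses laboratory measurement.

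**Expected NAC effect.** From a pooled analysis that did not include MDR-TB patients, the Discussion reports nausea, vomiting and "abdominal pain which increased 1.4–2.2 times compared to those that did not get NAC".

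**The concern.** The comparison is meant to show whether NAC protects against the toxicity of the second-line drugs. Control patients receive no NAC, so any event NAC causes can arise only in the NAC arms. If such events are counted as ADRs, the endpoint adds NAC's harm to the toxicity it is meant to prevent, and the difference shrinks or reverses. The Background and rationale section describes GI effects as common with the second-line regimen too, so the same symptom could be assigned to either drug.

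A second problem does not depend on which drug is meant. An event becomes an ADR only when an investigator who knows the arm judges it related. If the chance of being called related differs by arm, the ADR proportions differ even where the event rates do not, and the direction cannot be predicted. The results are intended to guide a later trial, so a diluted or distorted estimate would carry into its design.

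**Working it through.** **Figures in the plan.** The article gives no ADR rate, effect size, alpha or power. The only related figure is the sample size (20 × 3 = 60, and 60 × 1.10 = 66), which does not bear on this point. The check is therefore a sensitivity calculation.

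**Formula.** Let *t* be the proportion with organ toxicity and *g* the proportion with a GI ADR, assumed independent. Then P(any ADR) = 1 − (1 − t)(1 − g). In the NAC arm, g is the control value times a ratio R. R = 1.0 means NAC causes no extra GI events, or that they are not counted. R = 1.4 and 2.2 are the ends of the range in the Discussion.

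**Illustration.** Toxicity of 45% in control and 30% with NAC is assumed and stands nowhere in the article. The control GI rate of 14% is the bedaquiline figure in Background and rationale.

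- Control: 1 − 0.55 × 0.86 = 52.7%
- NAC, R = 1.0: 1 − 0.70 × 0.86 = 39.8%; difference 12.9 points
- NAC, R = 1.4: g = 0.196; 1 − 0.70 × 0.804 = 43.7%; difference 9.0 points
- NAC, R = 2.2: g = 0.308; 1 − 0.70 × 0.692 = 51.6%; difference 1.1 points

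The comparator is 12.9, not the 15-point difference in toxicity. Background GI events alone mask about 2 points (15 − 12.9 = 2.1), and only the remaining loss is due to NAC.

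**Range from rates in the article.** The drug-induced liver injury rates without NAC are 14.3% and 37.5%, from the two drug-susceptible TB trials in Background and rationale. Each is either halved or abolished by NAC. Control GI rates are 14% (bedaquiline) and 22% (clofazimine, a figure that also covers skin discolouration). Entries are control minus NAC in percentage points; break-even is the R at which the difference is zero.

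| Toxicity, control → NAC | GI in control | R = 1.0 | R = 1.4 | R = 2.2 | Break-even R |
|---|---|---|---|---|---|
| 14.3% → 7.15% | 14% | +6.1 | +0.9 | −9.4 | 1.47 |
| 14.3% → 7.15% | 22% | +5.6 | −2.6 | −18.9 | 1.27 |
| 14.3% → 0% | 14% | +12.3 | +6.7 | −4.5 | 1.88 |
| 14.3% → 0% | 22% | +11.2 | +2.4 | −15.2 | 1.51 |
| 37.5% → 18.75% | 14% | +16.1 | +11.6 | +2.5 | 2.42 |
| 37.5% → 18.75% | 22% | +14.6 | +7.5 | −6.8 | 1.82 |
| 37.5% → 0% | 14% | +32.3 | +26.7 | +15.4 | 3.30 |
| 37.5% → 0% | 22% | +29.2 | +20.4 | +2.8 | 2.33 |

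In five of the eight rows the break-even ratio lies within or below 1.4–2.2, so a real benefit can be cancelled or reversed. In the other three it is diluted but not reversed.

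**The case against.** **The definition may already exclude NAC.** Relationship to the IMP is recorded separately, and elsewhere the article uses ADR for reactions to second-line drugs, for example in the endpoint on regimen changes due to ADRs. A reader might infer that NAC's reactions certainly count as endpoint events. The text does not support that; it is ambiguous. The objection stands to that extent, but nothing states the exclusion, and applying it would still depend on attribution by staff who know the arm.

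**Other analyses avoid most GI symptoms.** A laboratory-based efficacy analysis would leave out most nausea, vomiting and abdominal pain. Hypotheses I and II concern serious events, and severe ADRs by CTCAE are analysed separately; mild intolerance would enter neither. This limits the problem, but the laboratory statement conflicts with the Primary objective and Concealment mechanism sections.

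**A net-effect endpoint is legitimate.** Counting NAC's harm alongside its benefit answers a real question about total ADR burden. That is right, but it is a different question from organ protection and would have to be stated as the target. Nor does it follow that any result would be uninterpretable, since the components can be reported separately.

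**Events related to experimental treatment.** A reader might call this safety endpoint flawed because it must be empty in control. It is not: it describes tolerability and allows the two NAC doses to be compared.

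**It is a pilot.** There is no formal power calculation, and the Primary endpoint section lists feasibility metrics, although Trial design and Concealment mechanism name ADRs. This tempers the consequence, but the ADR estimate is still meant to inform the next trial.

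**Conclusion.** The point holds as an ambiguity and a conflict, not as a certainty that NAC's reactions are counted. The ADR definition leaves the drug unnamed, attribution is made with knowledge of the arm (the blinding text contradicts the open-label statements and cannot be relied on), and the sections disagree on whether the efficacy endpoint is clinical and laboratory or laboratory only.

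The dilution is conditional on clinical ADRs counting and NAC-related GI events not being excluded. In the illustration it takes 12.9 points down to 9.0 or 1.1. Across rates taken from the article, the outcome runs from dilution to reversal. These sizes rest on independence of toxicity and GI events, an assumed 45% to 30% fall or liver-injury rates from drug-susceptible TB in older patients, single-drug GI rates, and a GI ratio from studies without MDR-TB patients. The risk of attribution bias, in either direction, needs none of these assumptions. The matter should be corrected before analysis.

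**What to change.** Reconcile the Primary objective, Concealment mechanism and Adverse event reporting sections with the statistical methods:

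1. Base the efficacy comparison on laboratory and ECG abnormalities at a stated CTCAE grade, counted the same way in all arms regardless of attributed cause.
2. Report GI and other clinical events, from all causes, separately by arm as tolerability or supporting endpoints.
3. Keep investigator causality, including relationship to the IMP, as descriptive only, and say which drug each relationship field refers to.
4. Resolve the contradiction between the open-label and blinding statements.

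The first two steps are needed together. Counting all events regardless of cause removes attribution bias, but applied to a composite that still contains GI symptoms it would leave the dilution in place.

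The cost is endpoint wording and programming, since the safety laboratory tests, ECGs and event records are already planned. The downside is that purely clinical ADRs such as neuropathy move from the efficacy endpoint to a supporting one.
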